## Abstract

**Background:**

^18^F-FDG brain PET is clinically used for differential diagnosis in cognitive dysfunction of unclear etiology and for exclusion of a neurodegenerative cause in patients with cognitive impairment in late-life psychiatric disorders. ^18^F-FDG PET measures regional glucose metabolism, which represents a combination of neuronal/synaptic activity but also astrocytic activity and neuroinflammation. Recently, imaging of synaptic vesicle protein 2 A (SV2A) has become available and was shown to be a proxy of synaptic density. This prospective study will investigate the use of ^18^F-SynVesT-1 for imaging SV2A and its discriminative power for differential diagnosis in cognitive disorders in a head-to-head comparison to ^18^F-FDG PET. In addition, simultaneous PET/MR allows an evaluation of contributing factors and the additional value of advanced MRI imaging to FDG/SV2A PET imaging will be investigated. In this work, the study design and protocol are depicted.

**Methods:**

In this prospective, multimodal imaging study, 110 patients with uncertain diagnosis of cognitive impairment who are referred for ^18^F-FDG PET brain imaging in their diagnostic work-up in a tertiary memory clinic will be recruited. In addition, 40 healthy volunteers (HV) between 18 and 85 years (M/F) will be included. All study participants will undergo simultaneous ^18^F-SynVesT-1 PET/MR and an extensive neuropsychological evaluation. Amyloid status will be measured by PET using ^18^FNAV4694, in HV above 50 years of age. Structural T1-weighted and T2-weighted fluid-attenuated inversion recovery MR images, triple-tagging arterial spin labeling (ASL) and resting-state functional MRI (rs-fMRI) will be obtained. The study has been registered on ClinicalTrials.gov (NCT05384353) and is approved by the local Research Ethics Committee.

**Discussion:**

The main endpoint of the study will be the comparison of the diagnostic accuracy between ^18^F-SynVesT-1 and ^18^F-FDG PET in cognitive disorders with uncertain etiology and in exclusion of a neurodegenerative cause in patients with cognitive impairment in late-life psychiatric disorders. The strength of the relationship between cognition and imaging data will be assessed, as well as the potential incremental diagnostic value of including MR volumetry, ASL perfusion and rs-fMRI.

## Background

Several neurodegenerative disorders can lead to dementia, including Alzheimer’s disease (AD), frontotemporal dementia (FTD), dementia with Lewy bodies (DLB), vascular dementia and other less frequent disorders. To aid in the differential diagnosis of patients presenting with a cognitive disorder, the consequences of neuronal dysfunction and death can be measured by imaging.

In clinical practice, most often ^18^F-fluorodeoxyglucose (FDG) PET or structural magnetic resonance imaging (sMRI) (e.g. by hippocampal volume assessment in AD) are used. ^18^F-FDG PET is healthcare-reimbursed in several countries for differential diagnosis in cognitive dysfunction of unclear etiology, and shows high sensitivity and specificity [1]. However, ^18^F-FDG PET has a disadvantage that regional glucose metabolism is a composite signal, consisting of a combination of neuronal and astrocytic activity [2], is partly determined by functional interconnectivity with other brain areas, and can be increased by local neuroinflammation. As the latter is present in all forms of neurodegeneration, a specific measure of regional neuronal impairment may thus be masked. Furthermore, acquisition circumstances (e.g. glucose blood concentration [3, 4]) and sensory stimulation during the tracer uptake period (e.g. light or noise), may influence the regional activity in sensory brain areas. In particular, medial temporal hypometabolism is variable and can be absent in many patients [5–7]. ^18^F-FDG is also not specific in the differential diagnosis between psychiatric disorders and neurodegeneration such as for behavioral variants of FTD [8]. Nonetheless, some studies have shown that ^18^F-FDG PET correlates with dementia severity [9, 10], and a correlation of neurocognitive parameters with regional changes in ^18^F-FDG uptake has been demonstrated [11]. Interestingly, in patients with subjective cognitive impairment (showing no significant deficits on neuropsychological testing), heterogeneous patterns of hypometabolism can be observed [12, 13] and also in cognitively normal patients with depressive symptoms AD-like hypometabolism has been reported, independently of amyloid burden [14]. Longitudinal studies will have to further clarify the meaning of these findings. sMRI is a widely available but a less sensitive marker with also relatively low specificity [15, 16] and quantification of hippocampal volume is not widely performed in clinical routine [17, 18]. While it is known that brain perfusion is a less sensitive marker for neuronal activity changes in neurodegeneration compared to ^18^F-FDG PET, and glucose uptake impairment is an earlier biomarker [19], brain perfusion techniques such as arterial spin labeling (ASL) are investigated as absolute regional blood flow and can be easily obtained in conjunction with other primary structural MR sequences [20–22]. The reported sensitivity and specificity of ASL for discrimination of patients from healthy volunteers (HV) varies from 53 to 86% and 84–92%, respectively [23, 24]. Differences in ASL technique and small sample sizes may be the main factors for this wide range, especially in sensitivity. Nevertheless, it has been suggested that ASL could replace the need for ^18^F-FDG and allow for another PET biomarker to be measured at the same time in PET/MR [21].

Until recently, measuring synaptic density in humans required brain tissue from autopsy or surgical resection specimens. In vivo PET imaging of synaptic density has now become possible through development of radioligands with high affinity and selectivity for synaptic vesicle protein 2 A (SV2A) [25], which is the only of three isoforms that is ubiquitously and homogeneously located/expressed in synapses across the brain. ^11^C-UCB-J has been thoroughly validated and is regarded as best-in-class ligand for SV2A/synaptic density PET imaging. ^11^C-UCB-J shows good pharmacokinetics, quantification of ^11^C-UCB-J distribution volume is possible and is an vivo proxy of synaptic density [26, 27]. ^11^C-UCB-J has been used in clinical epilepsy drug trials [28]. Simplified quantification with a white matter reference is possible for easier use in patient populations [29, 30]. Furthermore, stability of synaptic density in healthy aging has been shown [31, 32]. A direct comparison in young HV, has shown differences between resting ^18^F-FDG uptake patterns and the regional distribution of synaptic density, with relative differences up to 30% with higher ^11^C-UCB-J signal especially in the hippocampus, lateral temporal cortex and cingulate, areas of particular importance in cognitive impairment [33].

Pilot studies in patients with AD show a medial temporal decrease in synaptic density of up to 40% compared to HV [34–37], while in the neocortex more moderate changes of about 10% are present whereas for ^18^F-FDG these are about 20% [38]. In a direct comparison, medial temporal ^11^C-UCB-J signal showed strongest correlations across all cognitive domains whereas for neocortical regions, ^18^F-FDG uptake seems more strongly correlated [39]. In mild cognitive impairment (MCI) there is a strong negative relationship between synaptic density and hippocampal tau accumulation [40, 41], while in MCI and AD, SV2A binding is also highly correlated with several cognitive domain functions [37, 40–42]. In FTD subtypes, which are mainly associated with aberrant TDP-43/tau/FUS protein depositions, distinct patterns of synaptic loss compared to other neurodegenerative disorders have been observed in populations including C9orf72 mutation carriers [43], behavioral variant FTD [44], PSP and CBD [45, 46]. Multimodal imaging has revealed an association between lower synaptic density and reduced functional connectivity, in addition to that accounted for by grey matter atrophy [47]. In Lewy body dementia, including Parkinson’s dementia and DLB, deposits of alpha-synuclein form the main underlying proteinopathy and compared to Alzheimer’s disease, there is often only mild atrophy. Also in this population, marked cortical synaptic loss can be observed [48, 49].

The short half-life of ^11^C (20.4 min) and single tracer manufacturing per subject makes the clinical routine use of ^11^C-UCB-J cumbersome. Recently, ^18^F-SynVesT-1, an optimized ^18^F-labeled analogue of UCB-J with similar kinetics, binding, and test-retest properties has been evaluated in humans [50–52] with also good quantitative correspondence to ^11^C-UCB-J.

The primary objective of this clinical trial is to determine the added value for clinical use of synaptic density imaging using a multimodal simultaneous PET/MR approach in patients with dementia and other patients developing cognitive dysfunction, by assessing the functional burden of the disease on the level of the synapse instead of synaptic activity/glucose metabolism, and by identifying an optimal combination of synaptic density and other PET/MR imaging metrics (perfusion, structural atrophy) that may allow early assessment and risk stratification for cognitive and behavioral dysfunction in de novo patients with uncertain origin of dementia. This will enable us to better understand the underlying pathophysiology of dementia, assess the direct consequences of underlying proteinopathy, relate this to subsequent structural measures and identify those parameters that can contribute to the accuracy of an early differential diagnosis. It will thereby aid the societal/economic challenge of earlier diagnosis, prognosis and biomarker development for more objective and more efficient monitoring of novel therapeutic trials. Secondary objectives are to assess how synaptic density is altered in the different cognitive disorders and how it correlates to specific symptomatology. Moreover, a direct comparison between ^11^C-UCB-J and ^18^F-SynVesT-1 in terms of distribution volume and standardized uptake value ratios (SUVR), including variability and noise levels will be conducted in HV.

## Methods and analysis

### Study design

This is a prospective and multimodal imaging study that aims to investigate and compare the discriminative power of ^18^F-SynVesT-1 PET and the standard-of-care ^18^F-FDG PET in differential diagnosis for cognitive disorders. Study approval has been obtained by the ethics committee at the University Hospitals Leuven and by the Belgian competent authority (federal agency for medicines and health products (FAMHP) as well as the federal agency for nuclear control (FANC)). It will be conducted in accordance with the latest version of the Declaration of Helsinki as well as the Good Clinical Practice guidelines and all applicable regulatory requirements. The collection, processing and disclosure of personal data, such as patient health and medical information is subject to compliance with applicable personal data protection and the processing of personal data (General Data Protection Regulation and the Belgian Law on the protection of natural persons with regard to the processing of personal data). The study has been registered on ClinicalTrials.gov (NCT05384353).

### Study hypotheses

The following specific research questions will be addressed:

(i)Can SV2A PET, using the novel tracer ^18^F-SynVesT-1, be approximated quantitatively by means of a simplified reference tissue model in HV and is it quantitatively comparable to ^11^C-UCB-J?(ii)Are there regional differences between SV2A PET and ^18^F-FDG PET and do the patterns remain unchanged versus HV?(iii)Can ^18^F-SynVesT-1 PET detect various forms of dementia as accurately as ^18^F-FDG PET?(iv)Does a combination of ^18^F-SynVesT-1 PET with MR-based markers of structural abnormalities and arterial spin labeling allow a better discrimination of different forms of dementia?

Based on literature and current knowledge, the following hypotheses are formulated:

(i)Healthy aging does not result in reduced synaptic density in adults up to 85 years. ^18^F-SynVesT-1 may show a better signal-to-noise ratio and at least equivalent utility for clinical applicability compared to ^11^C-UCB-J.(ii)Simplified quantification of ^18^F-SynVesT-1 PET is possible with white matter (centrum semiovale) as reference region [30, 53] or cerebellum as pseudo-reference region [42].(iii)Synaptic density and arterial spin labeling, as indirect marker of neuronal activity, are related in absolute terms in healthy agers, while regional differences are present that may affect the sensitivity of detection of pathological consequences.(iv)^18^F-SynVesT-1 PET allows accurate detection of patients with an underlying pattern specific for Alzheimer’s disease, frontotemporal dementia and Lewy Body disease, and can discriminate these neurodegenerative diseases from healthy aging and patients with cognitive impairment due to late-life psychiatric disorder.(v)^18^F-SynVesT-1 PET has non-inferior sensitivity and specificity of diagnosis in comparison to ^18^F-FDG PET.(vi)Non-invasive determination of absolute ^18^F-FDG glucose metabolism, ASL and SV2A (SUVR) allows discrimination of patients with late-life psychiatric disorder and neurocognitive disorders with highest accuracy for synaptic density imaging.(vii)Synaptic density PET is better correlated to memory and executive neurocognitive tests compared to ^18^F-FDG PET or ASL, especially in the frontal and medial temporal cortex.

### Study participants

A total estimated cohort of 110 patients with uncertain diagnosis of cognitive impairment that are sent for ^18^F-FDG PET brain imaging in their clinical-diagnostic work-up will be recruited from the memory clinic of the University Hospitals Leuven, Belgium. This includes patients who do not yet have a final diagnosis at study inclusion but do show objectified cognitive impairment on neuropsychological evaluation as to avoid the inclusion of patients with subjective cognitive decline that have a lower likelihood of underlying neurodegenerative disease. All included patients will thus suffer from MCI (amnestic or non-amnestic) or dementia, according to the Diagnostic and Statistical Manual of Mental Disorders (DSM-V) criteria (respectively mild or major neurocognitive disorder) [54]. An initial working diagnosis is made by the clinician based on clinical workup, neuropsychological testing, biomarker tests (for AD suspicion: CSF Aβ42/Aβ40 and total tau or amyloid PET if no CSF) and sMRI. Patients with uncertain diagnosis are referred for ^18^F-FDG PET. From this population patients are recruited for the proposed research. ^18^F-SynVesT-1 scanning will be done as soon as possible, within maximally 3 months from ^18^F-FDG PET.

Patient inclusion criteria are:

(i)Patients referred with uncertain diagnosis of cognitive impairment and subsequent need for ^18^F-FDG PET in their work-up to differentiate between neurocognitive disorders or to exclude a neurodegenerative disorder in late-life psychiatric disorders with cognitive impairment.(ii)A routine neuropsychological assessment has been performed during clinical work-up in the memory clinic.(iii)Subject is at least 30 years old.

Main patient exclusion criteria are:

(i)Subject has a history or evidence of other major neurological, major psychiatric or major internal pathology (including cardiac, lung, hematological, gastro-intestinal disorders or most forms of cancer).(ii)Subject’s neurological condition has a predominant impact on motor function.(iii)Subject has no objective cognitive-behavioral deficit based on neuropsychological assessment.(iv)Subject has important vascular changes abnormal for age or other structural lesions on MR.(v)Subject is currently a user (including ‘’recreational use’’) of any illicit drugs, including cannabis, or has a history of drug or alcohol abuse.(vi)Subject has a contra-indication for MRI scanning.(vii)Subject suffers from claustrophobia or cannot tolerate confinement during PET-MRI scanning procedures; subject cannot lie still for 30 min inside the scanner.(viii)Subject does not understand, is unwilling or unable to perform the study procedures or does not have a guardian who understands the study procedures.(ix)Subject is pregnant (according to Ulti Med hCG urine test) or breastfeeding. For women of childbearing potential: subject does not not agree to apply appropriate contraception methods during study participation and continues to do so for at least 6 months after study completion.

For comparison, we will also include a sample of 40 HV between 18 and 85 years old who have no prior or current medical, psychiatric or neurologic illness as determined by review of medical history as well as extended clinical and neuropsychological assessment. In addition, for subjects below 60 years of age, an unremarkable structural MRI scan is expected whereas for subject above 60 years of age, a Fazekas of < 2 is accepted. Main exclusion criteria of patients also apply to the HV series. However, subjects on anticoagulant therapy or who chronically use medication with effects on the central nervous system will be excluded from the HV sample. Of this HV cohort, 10 subjects will also be subjected to a ^11^C-UCB-J PET in order to assess the quantitative comparability with ^18^F-SynVesT-1.

#### Sample size

Taking into account the test-retest variability for ^18^F-SynVesT-1 (5–10%) [52]; and a non-inferiority margin of 10%, assuming an α-level of 0.025 and a statistical power of 80%, the required sample size is 8 patients, of no ‘true’ difference. As sensitivity analysis, in case this difference would be 1% or 2%, sample sizes would increase to 10 and 12 per group.

Moreover, the sample size for brain receptor single-center PET studies using absolute quantification as we do in healthy subjects is typically between 10 and 20 in most literature studies. We include 40 healthy controls and 110 patients with estimated subgroups sizes of 50 amnestic mild cognitive impairment (aMCI)-AD, 20 FTD, 20 DLB and 20 patients with late-life psychiatric disorder based on our referral data.

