Statistical analyses will be performed using GraphPad Prism version 9 (GraphPad Software, La Jolla, CA). Demographic characteristics will be compared between groups using an unpaired Student t-test, unpaired Mann-Whitney U test, Fischer’s exact test or Chi-square test for trend as appropriate. Data normality will be verified by a Shapiro-Wilk test (α = 0.05). Correlation analyses will be performed by a Pearson correlation if data are normally distributed or by a Spearman correlation if data do not follow a normal distribution. Paired student’s t-tests or a non-parametric substitute will be performed in both a voxel-based and a VOI-based analysis to investigate regional differences between ^18^F-SynVesT-1 PET and ASL. Signature patterns of reduced synaptic density for different cognitive disorders will be assessed by comparing ^18^F-SynVesT-1 in patient subgroups versus HV using Student’s t-tests or Mann Whitney U-tests. To explore the diagnostic performance of ^18^F-SynVesT-1 compared to ^18^F-FDG, scans will be visually assessed by different specialists in nuclear medicine/neurologists and diagnostic accuracy (sensitivity, specificity and accuracy) as well as the interobserver agreement will be calculated. All results will be adjusted for multiple comparisons (Bonferroni) and investigated two-sided at a significance level of 0.05.

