The sample size calculation was based on observed effect sizes for ^11^C-UCB-J as ^18^F-SynVesT-1 data are not yet publicly available. However, similarity of ^11^C-UCB-J and ^18^F-SynVesT-1 in terms of distribution volume and binding potential as well as test-retest characteristics has been demonstrated [51, 52]. Accordingly, it can be expected to find similar effect sizes for ^18^F-SynVesT-1 as for ^11^C-UCB-J and we believe the anticipated sample size will result in adequate power. Another limitation will be the short acquisition protocol for the patient group and the associated simplified quantification method (SUVR), which was a trade-off between scanning a larger sample with simplified quantification or a smaller sample with full dynamic quantification. Of note, performing 90-minute dynamic acquisitions in a clinical setting is not feasible. As we aim to investigate the clinical applicability of ^18^F-SynVesT-1, the use of short static acquisitions is justified. The single-tracer nature of the study can be seen as a limitation since we cannot for example determine correlations with tau or amyloid PET imaging data. Nevertheless, ^18^F-FDG PET data will be acquired for clinical work-up in all patients (as inclusion criteria) and most patients will also receive lumbar punctions to determine cerebrospinal fluid levels of Aβ42/Aβ40 and total tau to exclude or confirm AD. Therefore, performing retrospective (sub)analyses using these data might also be possible upon study completion and ethics approval.

In conclusion, this study will provide further insight into synaptic density PET and its diagnostic applicability in a clinical routine setting.

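### The only sample-size calculation sizes a continuous uptake measure, so its 80% power does not apply to the main endpoint, the paired comparison of diagnostic accuracy

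*Protocol article*

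**What the plan says.** The Discussion part of the abstract fixes the endpoint: "The main endpoint of the study will be the comparison of the diagnostic accuracy between" the two tracers, including the exclusion of neurodegeneration in late-life psychiatric disorder. Hypothesis (v) under Study hypotheses makes this a non-inferiority claim: 18F-SynVesT-1 "PET has non-inferior sensitivity and specificity of diagnosis in comparison to" 18F-FDG PET. Under Data analysis and statistics, scans are assessed visually and "diagnostic accuracy (sensitivity, specificity and accuracy) as well as the interobserver agreement will be calculated".

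The Sample size section opens with "Taking into account the test-retest variability for" 18F-SynVesT-1, given as 5–10%. It adds a 10% non-inferiority margin and concludes: "assuming an α-level of 0.025 and a statistical power of 80%, the required sample size is 8 patients" if there is no true difference. For a true difference of 1% or 2%, "sample sizes would increase to 10 and 12 per group". The section then gives 40 healthy volunteers and 110 patients (about 50 aMCI-AD, 20 FTD, 20 DLB and 20 late-life psychiatric), with subgroup sizes taken from referral figures.

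The limitations part of the Discussion describes the basis differently: "The sample size calculation was based on observed effect sizes for" 11C-UCB-J. It goes on to state a belief that the planned sample gives adequate power.

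**The concern.** Every patient has both scans, so sensitivity and specificity are compared through paired correct/incorrect reads. The variance of that comparison depends on how often the two tracers lead to different calls. It does not depend on the test-retest noise of an uptake value. The Sample size section gives no sensitivity, specificity or discordance rate, so its 80% power belongs to another quantity. Hypothesis (v) is the only hypothesis worded as non-inferiority, and the section speaks of patients, so a reader will naturally attach the figure to it.

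If hypothesis (v) is not met, especially for specificity, the published text would suggest a trial with ample power. In fact no power for that comparison has been stated. The two descriptions of the basis also cannot both be right, so the calculation cannot be checked as reported.

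**Working it through.** **1. Reproducing the plan's figures.** Inputs from the Sample size section: margin 10%, alpha 0.025 (read as one-sided), power 80%, true difference d = 0, 1 or 2%, variability 5–10% (the exact SD is not stated).

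Two-group non-inferiority for means: n per group = 2·SD²·(1.960 + 0.842)²/(10 − d)², with (1.960 + 0.842)² ≈ 7.849.

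With SD = 6.9%:
- d = 0: 2 × 47.61 × 7.849/100 = 7.47, so 8
- d = 1: 2 × 47.61 × 7.849/81 = 9.23, so 10
- d = 2: 2 × 47.61 × 7.849/64 = 11.68, so 12

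One SD inside the stated range gives all three figures, per group. A t-based version does the same with SD 6.5%. The choice of SD matters: at d = 0 the same formula gives 4 per group with SD 5% and 16 with SD 10%. The figures are a valid sample size for a mean.

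**2. The quantity in hypothesis (v).** For paired reads with no true difference, power ≈ Φ(m·√(n/ψ) − 1.960). Here m is the margin on the difference in proportions and ψ is the proportion of patients in whom one tracer's read is correct and the other's is not. Two inputs are assumptions. ψ is given nowhere, so a range is shown. The 10% margin is stated only in the calculation for a mean, so m = 0.10 on proportions is carried over.

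Example: n = 110, ψ = 0.10 gives 0.10 × √1100 − 1.960 = 1.357, so 91%.

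| Discordance ψ | All 110 patients (overall accuracy) | 90 neurodegenerative patients (sensitivity) |
|---|---|---|
| 10% | 91% | 85% |
| 15% | 77% | 69% |
| 20% | 65% | 56% |
| 25% | 55% | 48% |

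The 90 are 50 + 20 + 20. Reaching 80% power needs ψ ≤ n × 0.01/7.849, which is about 14% for 110 patients and 11.5% for 90.

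**3. Specificity against late-life psychiatric disorder (about 20 patients).** The normal approximation is unreliable at this size, so a score interval for the paired difference is used. If both tracers agree in all n patients, its lower bound is −z²/(n + z²):
- n = 20: −3.84/23.84 = −16.1 points, outside a 10-point margin
- the bound comes inside 10 points only when n > 9 × 3.84 = 34.6, so 35 fully concordant patients

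With 20 patients and no read favouring 18F-FDG, 18F-SynVesT-1 needs at least two discordant reads in its favour: the bound is −11.9 with one and −7.7 with two. Enumerating all outcomes under no true difference gives power of 6%, 11% and 13% at 5%, 10% and 20% discordance.

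**4. The two stated bases side by side.** The Sample size section uses test-retest variability of 18F-SynVesT-1 and contains no effect size and no 11C-UCB-J figure. The Discussion says the calculation rests on 11C-UCB-J effect sizes. Even if the second description were the right one, such effect sizes are differences in uptake and would still not size a comparison of accuracy.

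**The case against.** The best defence is that the arithmetic is right, that nobody intends to analyse 8 patients, and that 110 are enrolled. All of that stands. A reader might infer that 110 is too few, but the document does not support that: overall accuracy reaches 80% power if discordance is about 14% or less.

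It is also fair that no margin on sensitivity or specificity is stated anywhere, so the power figures rest on two assumptions. They are offered as a range for that reason.

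The limit of 20 patients applies to one contrast only. Readers choose among several diagnoses, so specificity for AD would use about 60 non-AD patients, and for FTD or DLB about 90. With 60 fully concordant patients the score bound is −3.84/63.84 = −6.0 points, inside a 10-point margin.

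Two further inferences are tempting and fail. The Background reports that "in the neocortex more moderate changes of about 10% are present whereas for" 18F-FDG they are about 20%; this might seem to contradict the assumed true differences of 0–2%. Those figures are uptake changes in AD against healthy volunteers, not differences in accuracy, and the Discussion itself argues that effect size need not decide discrimination. The move from 8 patients to 10 and 12 per group might look like a change of basis, but one SD reproduces all three per group, so it is loose wording.

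Finally, an article may leave a power table to the full protocol or analysis plan. That does not answer the point, because this article states a calculation, gives its basis in two incompatible ways and asserts adequate power.

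**Conclusion.** The point holds as a mismatch between calculation and endpoint, not as an arithmetic error. The stated 80% power applies to a continuous uptake measure. For the main endpoint no power has been stated, and the Discussion's claim of adequate power is unsupported for it. The Sample size section and the Discussion contradict each other on the basis.

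Under a 10-point margin on proportions, one-sided 0.025 and no true difference, power at the planned numbers runs from about 91% down to 55% for overall accuracy and from 85% down to 48% for sensitivity, as discordance rises from 10% to 25%. Specificity against late-life psychiatric disorder is not powered for such a margin. The size depends on both the assumed margin and the assumed discordance; the mismatch and the contradiction depend on neither.

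**What to change.** - In Sample size, say which quantity the 8, 10 and 12 refer to, give the SD used, and state that all three are per group.
- Make Sample size and the Discussion give the same basis.
- Replace the power claim for hypothesis (v) with paired-binary non-inferiority power at the planned numbers. State the margin on the proportion scale and show a range of discordance, for example 10–25%.
- State that specificity against late-life psychiatric disorder is estimated with a confidence interval in about 20 patients and is not powered for a margin of that size.

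The cost is rewording two sections, with no extra patients. The drawback is that the stated power becomes less favourable. Whether overall correct classification should become the powered endpoint is a separate design choice for the sponsor and is not required here.
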